### Interventions and analysis

A complementary suite of methods correlates with each of the study objectives.

### Objective 1: Enhance the existing TSS case management approach by supporting a multi-component mentoring intervention for staff, and assessing its impact

Based on the evidence and feasibility of strengthening the current case management/mentoring approach of TSS, the research partnership identified the need for a multi-component suicide prevention mentoring approach to: 1) enhance the current workforce competencies of TSS staff through explicit empowerment and suicide awareness training (a tailored FWB and gate-keeper training); and 2) provide regular follow up support for mentors using reflective CBPR frameworks to continuously improve the mentoring approach and strengthen the capacity of TSS staff to mentor students (mentees) to modify the risk and protective factors for suicide.

*First*, we will refine a multicomponent mentoring suicide prevention training package for delivery to mentors. The investigator team has previously piloted the FWB as a single intervention and documented its acceptability, feasibility and outcomes. We will value-add by bolstering FWB delivery with gatekeeper training (Aboriginal and Torres Strait Islander Mental Health First Aid), resilience and mentoring training.

*Second*, The components of the training will be confirmed in collaboration with TSS but are likely to include: **1) Training in FWB 12 days**: Training will include FWB modules for examining and understanding human qualities, human needs, relationships, conflict and the process of change, emotions, crisis, beliefs and attitudes, family violence and loss and grief; **2) Gatekeeper training 2 days**: including suicide risk assessment and management; 3) **Resilience training 1 day**: including the nine things that young people need and how to build a resilience approach; and **3) Mentor training 0.5 days**: guidance for implementation of the mentoring approach to students to ensure implementation fidelity. With consent, baseline data, post-training and 6 month post-training data will be collected for TSS staff from surveys of wellbeing and confidence to implement the mentoring approach.

We will measure mentor changes in: 1) empowerment (benefits, stimulation, challenge and reward), and 2) confidence (understanding roles, commitment, and relationships of trust and respect) which are critical for effective mentoring relationships [36]. Measures are likely to include the Growth Empowerment Measure [50] and Participatory, Results-oriented, Self-evaluation (PROSE) tools [51]. Mentor changes in empowerment and confidence will also be measured using a tailored survey at baseline, post-training and at 6 months post-training.

*Third*, trained TSS staff will be engaged through CBPR critical reflexive sessions to define a resilience-based model of student support. The details of the model will be worked out in partnership with TSS, but it will be incorporate student workshops, learning plans, resilience strengthening and post-school aspirations. Opportunities for one-on-one and/or group mentoring will be identified. CBPR critical reflexive sessions will be continued over 30 months (continuous quality improvement in practice). Based on experience, 30 months is more than adequate to determine improvements. Feeding into CBPR processes will be baseline routinely collected and screening survey data (Objective 2), and evidence from the suicide prevention and mentoring literatures. Established questions will guide CBPR processes: how are we going; what is working, what is not; are we getting our fair share of resources relative to need; who is benefiting; who is missing out; what can be done to reach those people; how can we improve our situation. CPBR processes will be carefully documented. The continual improvement of the evidence-informed mentoring approach will contribute to shifting the focus of the current TSS case management approach from one of relative distance and constraints to a formalised mentoring relationship that provides support and capacity enhancement to students to negotiate their day to day challenges of life without being overwhelmed by them.

### Objective 2: Identify and apply valid and reliable quantitative outcome measures to assess the impact of the enhanced resilience-based service delivery model for Aboriginal and Torres Strait Islander students using an interrupted time series design

An interrupted time series design will be applied to evaluate the effects of the resilience-based training and redefined model of student support in modifying mentees’ resilience, educational outcomes, and suicidal risk. The research design provides practicality and rigour by staggering implementation of the mentoring approach, enabling each group to act as a comparison group for itself and the other group [52]. This design is endorsed by the Cochrane Effective Practice and Organization of Care Group as an alternative to randomised control trials. The design is based on randomisation of the primary and secondary schools and groups of de-enrolled students supported by TSS staff into three clusters where students supported by TSS will receive the resilience-based model of student support starting 2016; 2017 and 2018 (Fig. 2).

**Fig. 2 Fig2:**
[figure not shown]
Research deliverables

Selection criteria for the inclusion of schools will be collaboratively negotiated with TSS. The criteria will likely include: 1) having an enrolment of at least 10 TSS-supported students at the school and 2) being representative of the five TSS regions. We will also collect data for students from routinely available education indicators such as school attendance, retention. We will repeat the process with the second and third clusters of schools from 2017 to 2018.

We will assess the impact of the suicide prevention intervention on students’ resilience using: 1) routinely collected school outcomes data; and 2) screening survey data for the aggregated student cohort. Data routinely collected by Education Queensland (school attendance, retention and post-school destination) reflects suicide protective factors. Survey measures will be refined by the project steering group, but we anticipate a tailored instrument incorporating: resilience (individual capacities/ resources, relationships with primary caregivers and contextual factors that facilitate a sense of belonging), accompanied by the Kessler 5 psychological distress scale and suicidal risk factors, supplemented by questions assessing frequency of happy and angry feelings. Resilience will be measured using the Child and Youth Resilience Measure (CYRM) which has been validated internationally [53]. The suicide risk assessment questions are standard screening questions which were identified by a local Indigenous medical practitioner and CI as most relevant for Cape York students. The screening instrument will also include questions about services of which students are aware and access and transition strategies that they perceive to work. Using agreed measures, an online student screening survey will be integrated into TSS processes for student placements into boarding schools and administered using iPads to students in each cluster at the start of the 2016, 2017 and 2018 academic years.

Taking account of an expected drop-out rate of senior students who complete school; and the high likelihood of tracing students due to the close linkages between TSS staff with students and their families, we expect a follow up rate of 80 % at mid-point (*n* = 412) and 80 % at post-intervention (*n* = 330). These sample size calculations are based on population measures and study design. The primary outcome measures will be resilience (measured using the CYRM), and school participation (measured through routine data and including a composite indicator comprising uptake of placements at boarding schools at start of grade 7; uptake of the first scheduled flights to boarding schools each term; and a reduction in the rate of suspension for students who re-engage for issues that relate to not staying enrolled). Based on previously conducted studies using ANOVA for analysis, we assumed a 10 % effect size [53]. This is very conservative. We assumed a standard deviation of (0.3). Sample size calculations for an alpha level of 5 %, with power 80 %, *n* = 68 students per group, which will sufficiently enable statistical testing of the hypothesised differences. Since we had planned to sample *n* = 172 mentored students per group, about three times the sample size required, we are confident that our sample will be adequate for additional group-specific stratified analyses. The identified results of the routinely collected and screening survey data will be fed back to TSS staff to tailor the development of mentees’ aspirational plans. Following the baseline screening survey, the same instrument will be implemented at the end of the academic year and upon completion of the following two academic years.

A fixed cohort approach is planned [54] with the above-mentioned outcome measures for the 172 mentored students in group 1 compared pre- and post-intervention and to measures for the 172 students in groups 2 and 3. Separate statistical analyses will be undertaken for each outcome for each group using the statistical software program, STATA. The biennial proportion of students with each outcome of interest will be considered as a continuous measure for the analyses. Evaluation of the intervention effect in an interrupted time series design involves fitting a disjointed, segmented, linear regression model for the proportion of individuals with the outcome of interest over time, separately for each group. The models will include separate intercepts and slopes for both pre- and post-intervention (the two “segments”) and a term for site. For the intercepts, an intervention effect will be identified by a change or ‘jump’, in the primary outcome from pre- to post-intervention. For the slopes, an intervention effect will identified by a change in trend from pre- to post-intervention [55]. Examination of the magnitude of these coefficients will determine whether they are statistically significant.

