### The participants

We will work with TSS staff as mentors (24) and students as mentees (515) (*n* = 539). The mentors include all management, Transition Support Officers, Community Support Officers and Youth Mentors across the three streams of TSS: 1) transition from the primary to secondary phase of schooling; 2) engagement with secondary schooling and transition to work, training or further education at completion of Year 12; and 3) re-engagement with learning, training or employment pathways when enrolment at boarding schools is not an option. Mentees include the entire cohort of students assisted by the TSS: in 2015, 114 Year 7 students and families; 261 secondary school-aged students at boarding schools; and 140 students who have become de-enrolled from boarding schools and who have returned to their communities.

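### Two of the three parts of the school-participation composite do not fit the fixed-cohort, before-and-after regression planned for it

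*Protocol article*

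**What the plan says.** In the protocol article, under Objective 2, there are two primary outcomes: resilience on the CYRM, and school participation, which is taken from routine data and includes a composite indicator. The first two parts of that composite are "uptake of placements at boarding schools at start of grade 7; uptake of the first scheduled flights to boarding schools each term". The third part concerns suspensions and is worded as "a reduction in the rate of suspension for students who re-engage for issues that relate to not staying enrolled".

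The analysis paragraph of the same objective states "A fixed cohort approach is planned" and applies the outcome measures just listed to 172 students in each group. The analysed quantity is the proportion of students with each outcome over time. It is fitted by segmented regression, with separate intercepts and slopes before and after the intervention. The start years for the three groups are 2016, 2017 and 2018, after randomisation of schools and of groups of de-enrolled students.

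The section on participants gives the 2015 cohort: 114 Year 7 students, 261 secondary students at boarding schools, and "140 students who have become de-enrolled from boarding schools and who have returned to their communities". Re-engagement with learning, training or employment is one of the three streams of the service. Objective 2 also lists routine indicators outside the composite: "school attendance, retention and post-school destination".

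**The concern.** A fixed-cohort pre/post analysis needs an outcome that the same students can have, or not have, at each time point. It also needs a denominator that the intervention does not alter. Grade 7 uptake fails the first condition. The suspension part fails the second and, read literally, the first as well, because a reduction in a rate is a change in a group statistic and not a status that a student holds.

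If the plan is followed as written, movement in the composite may reflect which students are eligible for each part at each date and who has come back to school. The jump and the change in slope that the model is meant to detect would then not measure a change in participation of the cohort.

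**Working it through.** **The plan's own counts.** 114 + 261 + 140 = 515. 515/3 = 171.7, so 172 per group. Both agree with the article. The point does not rest on the sample size calculation.

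**The three parts against the fixed-cohort model.**

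| Part | Who can contribute | How often | Fit with a fixed cohort |
|---|---|---|---|
| Grade 7 placement uptake | Students entering grade 7; about 114/515 = 22.1%, or 114/3 = 38 per group | Once per student | No pre/post pair |
| First scheduled flight | Denominator not stated | Each term | Can be followed once a denominator is stated |
| Suspension | Students who re-engage; at most about 140/3 = 47 per group if they come from the 140 de-enrolled (assumption) | Repeatable after re-engaging | Set is formed after randomisation |

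**Grade 7 uptake.** If the 114 were already in Year 7 in 2015, their only value precedes every start date. If some enter later, each still has one value, on one side of the interruption. A series over calendar years would need new entrants each year, and that is not a fixed cohort.

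**Suspension, case mix alone.** The article gives no suspension or re-engagement rates, so all inputs here are assumed. Let 20 students re-engage with a 20% suspension risk, and let the programme bring back 20 more with risk p, leaving individual risk unchanged.

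Rate = (20 × 0.20 + 20 × p)/40 = 10% + p/2

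- p = 40%: 12/40 = 30%
- p = 30%: 25%
- p = 20%: 20%
- p = 10%: 15%

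The rate moves in either direction with no change in any student's risk.

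**Suspension, with a true benefit added.** Let re-engagement go from a₀ to a₁, with risk p₀ in usual and p₁ in additional re-engagers, and let the programme multiply every risk by c.

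Rate after = c × [a₀p₀ + (a₁ − a₀)p₁]/a₁

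The last column is the share of the baseline de-enrolled group that is re-engaged and not suspended, a × (1 − rate), before and after.

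| a₀ → a₁ | p₀ / p₁ | c | Rate among re-engagers | Re-engaged and not suspended |
|---|---|---|---|---|
| 30% → 60% | 15% / 40% | 0.9 | 15% → 24.8% | 25.5% → 45.2% |
| 30% → 50% | 20% / 40% | 0.9 | 20% → 25.2% | 24.0% → 37.4% |
| 30% → 45% | 20% / 30% | 0.9 | 20% → 21.0% | 24.0% → 35.6% |
| 30% → 60% | 20% / 25% | 0.8 | 20% → 18.0% | 24.0% → 49.2% |

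In the first row, with 47 de-enrolled students per group, those re-engaged without suspension go from 12.0 to 21.2 while the suspension rate rises. In the last row the rate falls, but only by a tenth although every risk was cut by a fifth.

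**A denominator that does not help.** Return to the example with p = 40%. Suspended students go from 4 to 4 + 8 = 12. Over all 172 in a group that is 4/172 = 2.3% to 12/172 = 7.0%, a tripling. A de-enrolled student cannot be suspended, so this measure looks best when nobody returns. Re-engaged and not suspended goes from 16/172 = 9.3% to 28/172 = 16.3% in the same example.

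**The case against.** The strongest reply is that a condensed article leaves scoring, weights, denominators and the handling of inapplicable parts to the full protocol or analysis plan. That is fair, and their absence is not the point here. What remains is that the article itself fixes the components, the fixed cohort and the proportion model, and these do not go together. A fuller document could resolve it only by changing one of them.

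Four stronger readings are tempting, and the document does not support them.

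- **That a primary outcome is lost.** School participation is said to include the composite, not to consist of it. Attendance and retention are collected separately.
- **That the three parts concern separate students, or that nobody can contribute to all three.** The sets overlap. A grade 7 entrant can take up a place and the first flight, and could leave and re-engage within the same year.
- **That first-flight uptake is undefined for the 140 de-enrolled students (27%).** Its denominator is not stated. They could be scored as no uptake, and any who return to boarding would have flights again.
- **That the composite gets worse when the programme works.** Only the suspension part is shown to be able to rise, under assumed risks, and one scenario gives a fall. The net direction of the composite depends on weights that the article does not give.

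It can also be said that the word reduction only names the hoped-for direction of an ordinary suspension rate. Granting that, the rate is still conditional on re-engaging.

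**Conclusion.** The concern holds for the composite as combined. Grade 7 uptake, relevant to about 22% of the cohort on 2015 counts, gives at most one value per student and so no pre/post contrast in a fixed cohort. This follows from the wording and needs no assumption. The suspension part is open to selection after randomisation. Its size and direction cannot be known from the document: under the assumed inputs the rate among re-engagers went from 20% to anything between 15% and 30% through case mix alone.

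The composite should therefore not be read as a fixed-cohort change in participation. First-flight uptake, attendance and retention can still be followed, and the resilience outcome is not touched. The change should be made because a primary outcome is affected, but it does not undermine the study as a whole.

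**What to change.** Do not combine the three parts in the fixed-cohort model. Instead:

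1. Analyse grade 7 placement uptake by successive entry-year intakes, outside the fixed cohort.
2. Analyse first-flight uptake each term on a stated denominator that is fixed before the intervention.
3. Replace the suspension rate among re-engagers with the proportion of a baseline-defined group who are re-engaged and not suspended. The group could be all students de-enrolled at baseline. It could also be all cohort members, with the outcome then read as in school and not suspended. More re-engagement cannot then by itself count as harm. Do not use suspensions over all cohort students.
4. Base the fixed-cohort analysis of school participation on a routine indicator defined for every cohort member at each time point, such as retention or attendance. Report students in work or training separately, since one stream of the service aims at those pathways and a school-only measure would otherwise record its successes as failures.

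The cost is the loss of the single composite and a few more outcomes to report. The fixed-cohort indicator uses data that the plan already names. Whether attendance can be had at each time point for students in all 34 destination schools is not shown and should be confirmed before it is chosen over retention.

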### Study aims

The 5 year study was developed in partnership with Education Queensland’s Transition Support Service (TSS) in response to increased suicide risk identified in transitioning students. It was funded by the National Health and Medical Research Council from December 2014. The study will investigate the impact of an enhanced multicomponent mentoring intervention to increase levels of psychosocial resilience among the 515 remote Aboriginal and Torres Strait Islander students from Cape York and Palm Island, who are compelled to relocate to boarding schools across Queensland when there is no secondary schooling provision in their home communities. We aim to test the null hypothesis that students’ resilience is not positively influenced by the multicomponent mentoring suicide prevention intervention. The objectives of this study are to:Enhance the existing TSS case management approach by supporting a multi-component mentoring intervention for staff and assessing its impact;Identify and apply valid and reliable quantitative outcome measures to assess the impact of the enhanced resilience-based service delivery model for Aboriginal and Torres Strait Islander students using an interrupted time series design;Apply cost analysis methods to calculate the economic costs of the intervention; andApply grounded theory methods to theorise and explain the process by which psychosocial resilience was enhanced to protect against suicide for Aboriginal and Torres Strait Islander students, including the contextual factors.

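### The stated 68 students per group is not reproduced by its own inputs (about 143 for a two-sided comparison of two groups), and the claimed threefold margin is wrong on the plan's own numbers

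*Protocol article*

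**What the plan says.** All the sample-size figures stand in one paragraph of the protocol article, under Objective 2 (Methods/Design).

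- **Effect:** "we assumed a 10 % effect size", introduced with "Based on previously conducted studies using ANOVA for analysis".
- **Spread:** "We assumed a standard deviation of (0.3".
- **Error rates:** "Sample size calculations for an alpha level of 5 %, with power 80" per cent.
- **Result:** "68 students per group, which will sufficiently enable statistical testing of the hypothesised differences".
- **Margin:** the plan is to sample "172 mentored students per group, about three times the sample size required". From this the authors conclude that "our sample will be adequate for additional group-specific stratified analyses".
- **Follow-up:** the same paragraph expects 80 % at mid-point (412 students) and a further 80 % at post-intervention (330 students).

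The paragraph does not say whether the test is one- or two-sided, on what scale the 10 % is measured, which contrast is powered, or whether a correlation between repeated measurements was used. The null hypothesis under Study aims is worded directionally: resilience "is not positively influenced by the multicomponent mentoring suicide prevention intervention". The next paragraph of Objective 2 compares group 1 before and after the intervention and also with groups 2 and 3.

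**The concern.** The article prints inputs, a result and a margin together, and they do not agree. Taken at face value, the result is less than half of what the usual two-group formula returns.

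The margin compares enrolment with the requirement, although the same paragraph expects about a third of the students to be lost by post-intervention. The plan to run stratified analyses rests on that margin.

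At stake is how a null result on resilience, a primary outcome, would be read. Someone relying on this paragraph would believe that the study had 80 % power with a large reserve. The stated inputs do not support that.

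**Working it through.** **Inputs (Objective 2, sample-size paragraph).** Alpha 0.05; power 0.80; SD 0.3; effect 10 %, read as an absolute difference of 0.10. That reading is an assumption, but it is the one that makes use of the stated SD. The standardised difference is 0.10/0.30 = 0.333.

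**Attempt to reproduce 68.**

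1. Two independent groups, two-sided: n = 2 × (1.960 + 0.842)² × (0.3/0.1)² = 2 × 7.85 × 9 = 141.3, so 142. The t-test gives 142.2, so 143.
2. Two independent groups, one-sided: n = 2 × (1.645 + 0.842)² × 9 = 111.3, so 112.
3. Within-student change, two-sided, with 0.3 taken as the SD of change: n = 7.85 × 9 = 70.6, so 71. The t-test gives 72.6, so 73.
4. One-way ANOVA with three groups: 132 per group if one group differs by 0.10; 175 if the means are equally spaced over 0.10.

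None returns 68. The nearest is the within-student test, which is not a comparison between groups.

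**What would be needed for 68.** A two-sided two-group test reaches 80 % power with 68 per group if the difference is 0.3 × 2.80 × √(2/68) = 0.144, or if the SD is 0.208. Alternatively, a baseline-adjusted analysis with one follow-up needs a correlation of √(1 − 68/141.3) = 0.72. The article states none of these.

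**Power at 68.** Two-sided, two groups: about 49 %. One-sided: about 61 to 62 %. Within-student: about 77 to 78 %.

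**The margin.**

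- Enrolment: 515/3 = 171.7, so 172 per group; 172/68 = 2.5.
- Mid-point: 515 × 0.8 = 412; 412/3 = 137 per group.
- Post-intervention: 412 × 0.8 = 330; 330/3 = 110 per group.
- 110/68 = 1.6 and 110/143 = 0.77.

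**Power for a difference of 0.10 with SD 0.3, two-sided t-test, no allowance for clustering:**

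| Contrast | Mid-point (137 per group) | Post-intervention (110 per group) |
|---|---|---|
| One group against one other | 78 % | 69 % |
| Group 1 against groups 2 and 3 combined | 89 % | 81 % |
| Within-student, 0.3 as SD of change | 97 % | 93 % |

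**Clustering.** Objective 2 randomises schools and groups of de-enrolled students, and the paragraph gives no design effect. For illustration only, assume an intracluster correlation of 0.01 to 0.05 and 10 to 25 students per cluster. The design effect 1 + (m − 1) × ICC then runs from 1.09 to 2.2, and 142 per group becomes 155 to 313. The power figures above are therefore optimistic.

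**The case against.** The strongest reply is that 68 may have a sound basis that the article does not report. The design follows a fixed cohort with repeated surveys, and repeated measures lower the requirement. With one baseline and two follow-ups, a baseline-adjusted comparison needs 141.3 × [(1 + r)/2 − r²] per group. This gives 70.6 at r = 0.50, 68.4 at r = 0.53 and 67.6 at r = 0.54, and it never exceeds 80. This stands as a possibility: a reader might infer a proven twofold arithmetic slip, and the document does not establish that. But the route needs a correlation and a number of follow-ups that the paragraph does not give. On the printed inputs alone, 68 cannot be obtained.

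The second reply is that a shortfall at follow-up is not shown, and this stands too. From 110 against 143 a reader might infer that the analysed groups are simply too small. That holds only for a two-sided pairwise contrast at post-intervention. Group 1 against groups 2 and 3 combined has 81 % power at that point, and a within-student test has 93 %. The clusters start in 2016, 2017 and 2018, so by the last survey all three have started. The contrasts of mentored with not-yet-mentored students come earlier, when fewer have been lost.

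The third reply is that 2.5 is loosely about three. At enrolment that could pass. It does not rescue the reserve, which is 1.6 times even the plan's own 68 once its own expected losses are applied.

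The article may condense a fuller calculation, but it prints these figures as they are, and a fuller document would not make the printed set consistent.

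**Conclusion.** The point holds in two parts.

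First, 68 per group is not reproduced by the stated inputs. The natural reading of a per-group figure with an SD gives about 143, roughly twice as many, and 68 then has about 49 % power. This assumes that 10 % means 0.10 on the scale of the SD, two-sided testing and independent groups. Relaxing sidedness gives 112 and relaxing independence gives 73, neither of which is 68.

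Second, the margin is wrong whichever test is used: 2.5 at enrolment and 1.6 at post-intervention, against a claim of about three. The confidence in stratified analyses loses its stated support.

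The documents do not support a flat statement that the study is underpowered. Unclustered two-sided power at 110 per group runs from 69 % to 93 % according to the contrast, and the calculation does not say which contrast it powers.

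**What to change.** In the sample-size paragraph of Objective 2:

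1. State the scale of the 10 % effect and of the SD (CYRM score or change in score), the sidedness, the test, the contrast and any assumed correlation.
2. Replace 68 with the figure these give; for a two-sided pairwise comparison it is 143 per group.
3. Report power for the contrast actually used at the numbers expected for analysis, 137 per group at mid-point and 110 at post-intervention. Examples are 78 % and 69 % pairwise, or 89 % and 81 % for group 1 against groups 2 and 3 combined. Say that these make no allowance for clustering, or add one with its assumed intracluster correlation.
4. Delete the statement that the sample is about three times the requirement, and label the stratified analyses exploratory.

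The cost is a less favourable set of printed figures. No extra students are needed and the design does not change.

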### The setting

TSS uses a case management approach based on a skilled helper mentoring model to support students from Palm Island and Cape York communities (Fig. 1): Weipa, Old Mapoon, Napranum, Aurukun, Pormpuraaw, Kowanyama, Lockhart River, Coen, Hope Vale, Cooktown, Laura, Rossville and Wujal Wujal to manage the transition challenges and develop opportunities that lead to Year 12 secondary leaving certificate attainment (or equivalent) and pathways beyond Year 12. TSS also engages with families, the 34 destination boarding schools from Weipa in the north of Queensland to Toowoomba in the south, and partner services (e.g. Families Responsibility Commission, Department of Communities, Juvenile Justice, Apunipima Cape York Health Council) that impact on students’ adjustment, orientation and ongoing stay at boarding school. However, issues for many students arise from the inadequacy of academic and social and emotional wellbeing preparation during primary school years and challenges in adjustment. These challenges resulted in 51 % of the 1026 Cape York students supported by TSS between 2008-March 2013 becoming de-enrolled and not returning to boarding school to complete their secondary schooling (Pers. Comm. AI [name], 10/10/2013). We do not know the precise levels of suicide or self-harm experienced by these students as there is no reliable data, but anecdotal evidence strongly suggests high levels of vulnerability e.g. since 2008, there has been three cases of suicide completion, 4 known hospitalisations for self-harm and ongoing concern about the normalisation of suicide ideation among some members of the cohort.

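### Sample adequacy and the fixed-cohort comparison rest on 172 students per group, but the plan's own follow-up leaves about 110 at post-intervention

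*Protocol article*

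**What the plan says.** All places are in the protocol article, Methods/Design.

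- **The participants:** "Mentees include the entire cohort of students assisted by the TSS". The 2015 figures are 114 Year 7 students, "261 secondary school-aged students at boarding schools" and 140 de-enrolled students.
- **Objective 2, allocation:** schools and groups of de-enrolled students are randomised into three clusters, which start the new support model in 2016, 2017 and 2018.
- **Objective 2, school selection:** the criteria are still to be negotiated, but will probably include "having an enrolment of at least 10 TSS-supported students at the school". The Setting section refers to "the 34 destination boarding schools from Weipa in the north of Queensland to Toowoomba in the south".
- **Objective 2, follow-up:** "Taking account of an expected drop-out rate of senior students who complete school", and counting on good tracing, the plan expects 80% at mid-point (412) and 80% at post-intervention (330).
- **Objective 2, sample size:** 68 students per group are required. The planned number is 172 "mentored students per group, about three times the sample size required", and this is the stated ground for confidence in further stratified analyses within groups.
- **Objective 2, analysis:** "A fixed cohort approach is planned", with outcomes for the "172 mentored students in group 1 compared pre- and post-intervention and to measures for the 172 students in groups 2 and 3".

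**The concern.** In a fixed cohort, a pre/post comparison uses students who are measured both before and after. The number that bears on adequacy is therefore the number followed up, and the plan gives it. Yet both the adequacy statement and the definition of the comparison use the number at entry. A reader would take the margin to be wider than it is, above all for stratified analyses, where each stratum holds only part of a group.

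Two further features bear on who is in the cohort. First, the staggered starts mean that a student close to the end of school may be exposed in group 1 but not in a later group. Second, a minimum school size, if adopted, conflicts with the statement that every TSS-supported student is included, and would lower 172 before any follow-up loss.

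**Working it through.** **Step 1. Reproduce the plan's figures.** Inputs are from The participants and Objective 2.

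- Cohort: 114 + 261 + 140 = 515.
- Per group: 515 / 3 = 171.7, rounded to 172. In reverse, 3 x 172 = 516, so 172 per group uses every student.
- Mid-point: 515 x 0.80 = 412, as stated.
- Post-intervention: 412 x 0.80 = 329.6, rounded to 330, as stated. The second 80% is thus taken of those at mid-point, and cumulative retention is 330 / 515 = 64%.

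**Step 2. Carry the follow-up to group level**, assuming that loss is even across the three groups.

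| Time | Total | Per group | Ratio to 68 |
|---|---|---|---|
| Entry | 515 | 172 | 172 / 68 = 2.5 |
| Mid-point | 412 | 412 / 3 = 137 | 137 / 68 = 2.0 |
| Post-intervention | 330 | 330 / 3 = 110 | 110 / 68 = 1.6 |

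The loss is 172 - 110 = 62 per group, or 36%. At no time is the ratio three.

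**Step 3. What this does to stratified analyses.** As an illustration, split each group into two equal strata and apply the plan's own 68 to each. At entry, 172 / 2 = 86, which exceeds 68. At post-intervention, 110 / 2 = 55, which does not. The article does not say which strata are meant, so the even two-way split is an assumption.

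**Step 4. Exposure by start year**, if the cohort is fixed at a 2016 baseline.

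| Year level in 2016 | Last school year | Group 1 (2016) | Group 2 (2017) | Group 3 (2018) |
|---|---|---|---|---|
| 12 | 2016 | exposed | finished before start | finished before start |
| 11 | 2017 | exposed | exposed | finished before start |
| 10 or lower | 2018 or later | exposed | exposed | exposed |

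The table assumes normal progression and continued enrolment. The article does not split the 261 students by year level, so the number affected cannot be derived.

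**Step 5. The school-size criterion.** Counting only the 261 boarders, 261 / 34 = 7.7 per school. At most 26 schools could then hold 10 or more, so at least 34 - 26 = 8 would be excluded. If the 114 Year 7 students also attend these schools, (261 + 114) / 34 = 11.0 and the arithmetic forces no exclusion. The article does not settle which count applies.

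**The case against.** The strongest defence is that nothing is hidden. The figures 412 and 330 stand beside the sample size calculation, they are said to allow for school completion, and 110 still exceeds the stated 68. That stands: on its own requirement the plan is not short of students for the main comparison. It does not rescue the threefold claim or the reliance on 172 for stratified analyses.

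Several stronger readings are tempting, and the documents do not support them.

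- **That attrition leaves the trial underpowered.** A reader might put a difference of 0.10 and an SD of 0.3 into a two-sample formula. That gives 142 per group (two-sided 5%, 80% power), which is above 110. But this reading does not reproduce the plan's 68. The nearest match is a paired two-sided test, at 71, and 110 exceeds that. Any shortfall would come from how 68 was obtained, which is a separate question.
- **That school leavers should be subtracted from 110.** The 80% rates already take account of them.
- **That loss differs between the randomised groups.** Under randomisation, seniors finish school at the same expected rate in every group. What differs is exposure before they finish. Nor does finishing school mean loss to follow-up: TSS supports students beyond Year 12, tracing is expected to work well, and post-school destination is routine data. A leaver could still complete the resilience measure.
- **That group 3 certainly contains unexposed leavers.** Objective 2 also says that the process will be repeated for the second and third clusters from 2017 to 2018. This could mean later baselines for those clusters, in which case earlier leavers would not be in them. The exposure point is therefore conditional.
- **That the 10-student rule removes a large, known share of students.** The rule is provisional, the distribution of school sizes is not given, and the de-enrolled students are randomised in their own groups, so a school rule may not touch them.

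**Conclusion.** The point holds as an internal inconsistency in a figure on which the plan relies. About 110 students per group, not 172, are expected at post-intervention. The margin over the stated requirement is 1.6-fold, against a claim of about threefold, and the figure at entry is itself only 2.5-fold. This rests on the plan's own retention figures and on even loss across groups. It takes 68 as given and does not endorse it. The confidence in stratified analyses is not supported as written.

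The exposure point is smaller and conditional on a cohort fixed at a 2016 baseline. It concerns unequal opportunity for exposure at school, and its size cannot be derived from the article. The coverage point is that two statements need reconciling; no number of excluded students can be put on it.

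**What to change.** 1. In Objective 2, restate the adequacy claim on about 110 per group at post-intervention (1.6 times 68). Define the fixed-cohort comparison on the students expected to be followed up. Withdraw the confidence in stratified analyses, or qualify it as exploratory. This is wording only.
2. State when the cohort is fixed for each group. If it is fixed at a 2016 baseline, add a sensitivity analysis restricted to students in Years 7 to 10 at the start of 2016, who are still of school age through 2018 whichever group they are in. The cost is a smaller sample, and year level must be recorded at baseline. It deals with school completion before the group's start, but not with de-enrolment.
3. Reconcile the whole-cohort statement in The participants with the provisional 10-student criterion in Objective 2. If the criterion is adopted, give the number of schools and students that remain and lower 172, and the follow-up figures derived from it, accordingly. This needs a count of TSS-supported students by school.
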